### Randomization and allocation concealment

The eligible participants will be allocated into 5 groups at a ratio of 1:1:1:1:1. Researchers of the Department of Reproduction of Zhangjiagang TCM Hospital Affiliated to Nanjing University of Chinese Medicine will use a random number generator of the Statistical Package for Social Sciences (SPSS) version 25.0 to carry out the randomization process. The random sequences will be put into several opaque paper envelopes, numbered sequentially and then distributed to clinical researchers and doctors [19]. When new patients are recruited in this trial, the opaque paper envelopes will be opened to decide their distribution; moreover, the researchers will arrange the corresponding interventions for the patients. All procedures above will be maintained and followed as appropriate.

### Blinding

This study is a single-blinded trial. Outcome assessors and people responsible for statistical analysis will be blinded to the randomization status.

### Data collection and management

Documentations such as paper case report forms (CRFs) will be applied to record relevant information (personal identity information, clinical data, etc.) of each participant. All medical information will be accurately recorded in the form of a double check by two researchers of the project team when inputted from the CRFs, monitored and validated by the data coordinating committee statisticians, and kept strictly confidential in a web-based electronic database, ResMan (www.medreaman.org), that needs special permissions. Information in the database and all original paper materials will be stored by a member of this trial who will never be involved in the clinical data collection throughout the whole process and the project team will ensure that the CRFs will be delivered securely to the Trial Office for data entry. All members of this study will keep the participants’ information confidential.

### Statistical analysis

Clinical data of all participants will be disposed in the final statistical analysis based on the intent-to-treat principle to determine the robustness of the evidence. The data processors will be unaware of the specific allocation situation. Basic indicators will be analysed to test the balance of each group at baseline. Comparisons will be processed based on changes from baseline to the end of the intervention and follow-up. The one-sample Kolmogorov-Smirnov test and graphical methods will be applied to test the normal distribution of continuous variables (such as the levels of basic serum sex hormones, HOMA-IR, ovulation rate, clinical pregnancy rate, BMI, FAI, Ferriman-Gallwey scores and TCM syndrome scores), which will be presented as the mean ± standard deviation if normally distributed and as the median with an interquartile range if not normally distributed. A paired *T* test or the Wilcoxon rank test will be used to compare variables within a group from baseline to the end of the intervention. Analysis of variance (ANOVA) with Bonferroni correction will be carried out to compare differences among groups of continuous variables consistent with a normal distribution. Continuous variables that do not meet the normal distribution will be processed by using the Kruskal-Wallis test followed by the Mann-Whitney *U* test. Categorical variables will be analysed by chi-square statistics when appropriate, and Fisher’s exact test will be used to compare discrete variables with fewer than 5 observations. All data analyses will be processed by the Statistical Package for Social Sciences (SPSS) version 25.0. A *P* value < 0.05 with a two-tailed test and mean difference with 95% confidence intervals will be considered statistically significant.

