#### Inclusion criteria

Chinese women aged from 18 to 35 years old.BMI [13] over 25.0 kg/m^2^.Confirmed diagnosis of PCOS according to the 2003 Rotterdam criteria [14]: (a) irregular menstruation cycles (a periodic interval > 35 days or < 8 cycles in a year) or amenorrhoea (a periodic interval > 90 days) or abnormal uterine bleeding; (b) clinical manifestations of hyperandrogenism (hirsutism in mainland China is taken as Ferriman-Gallwey score ≥5 [15]) and/or hyperandrogenemia [free androgen index (FAI)=total testosterone (nmol/L)/SHBG (nmol/L)×100 > 4.5 [16]]; and (c) transvaginal ultrasonography showing PCOM: the number of follicles with a diameter of 2–9 mm in one or both ovaries ≥12, and/or ovarian volume ≥10 ml [ovarian volume calculation: 0.5 × long diameter (cm) × diameter (cm) × anteroposterior diameter (cm)]. Among all the above, (a) is a necessary condition, and matching one of (b) or (c) represents suspected PCOS, which then requires ruling out other factors and diseases that may cause hyperandrogenism and ovulation dysfunction.In line with the diagnosis criteria of TCM syndrome differentiation: kidney deficiency and phlegm dampness.Confirming the diagnosis of insulin resistance: the criteria of IR are defined according to the homeostatic model assessment of insulin resistance (HOMA-IR) [fasting plasma glucose (mmol/l) × fasting serum insulin (uIU/ml)/22.5]. A value ≥2.29 [17] is considered to be indicative of IR.No history of using hormone drugs or drugs that affect glucose metabolism within the 3 months prior to treatment.Volunteer to participate in this trial and give informed consent.

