### Outcome measurements

#### Primary outcomes

The primary outcomes are changes in HOMA-IR (calculated according to the fasting plasma glucose and serum insulin) and improvements in the oral glucose tolerance test (OGTT) and insulin-releasing test (INS).

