### Sample size calculation

The sample size calculated by Power Analysis & Sample Size (NCSS-PASS 11.0) was assessed based on HOMA-IR, which is the most significant outcome in this trial. In our pilot study (according to the research results of [name] doctoral thesis) evaluating the effect of metformin and BSHTD on HOMA-IR in patients with IR-PCOS, the results showed that HOMA-IR decreased from 2.11±0.30 to 1.71±0.26 in the metformin treatment group and the difference before and after treatment was 0.40±0.24, while HOMA-IR of Bushen Huatan Decoction combined with metformin treatment group decreased from 2.09±0.30 to 1.52±0.26 and the difference before and after treatment was 0.57±0.27. Therefore, we used the minimum sample size required to evaluate effectiveness [18]. We anticipate that after two courses of treatment, HOMA-IR of Bushen Huatan Decoction combined with metformin group will decrease by 30%, and HOMA-IR of single-use of metformin group will decrease by 20%. Therefore, the difference is 10%,with two-sided α assigned to be 5% and *β* 20% at the upper limit, respectively, at which the power is 90% and the rate of attrition estimated to be 20%. In a one-way ANOVA study, sample sizes of 30, 30, 30, 30, and 30 were obtained for the 5 groups whose means are to be compared. A total sample size of 150 subjects achieves 90% power to detect differences among the means versus the alternative of equal means using an F test with a 5% significance level. By enrolling 38 participants in each group, we allow the rate of attrition to be estimated to be 20%.

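### Between-arm HOMA-IR comparison is valid but forgoes precision by not adjusting for baseline, and the within-arm paired tests cannot separate treatment effect from regression to the mean

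*Protocol article*

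**What the plan says.** The protocol's Primary outcomes section makes change in HOMA-IR a primary outcome: "The primary outcomes are changes in HOMA-IR (calculated according to the fasting plasma glucose and serum insulin". The Statistical analysis section sets the basis of comparison: "Comparisons will be processed based on changes from baseline to the end of the intervention and follow-up". It lists HOMA-IR among the continuous variables and names the tests.

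- Between arms, if normally distributed: "Analysis of variance (ANOVA) with Bonferroni correction will be carried out to compare differences among groups of continuous variables".
- Between arms, otherwise: "processed by using the Kruskal-Wallis test followed by the Mann-Whitney *U* test".
- Within each arm, a paired t or Wilcoxon test that "will be used to compare variables within a group from baseline to the end of the intervention".

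No baseline covariate is named. The Inclusion criteria select on the outcome variable itself: "A value ≥2.29 [17] is considered to be indicative of IR". All five arms in the Interventions section receive metformin, BSHTD, Baduanjin or a combination, so none is untreated.

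**The concern.** There are two separate issues.

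**Precision.** Eligibility rests on HOMA-IR and the outcome is change from baseline, so every participant has a baseline value. An unadjusted change score in effect fixes the baseline slope at 1. When the true slope is below 1, this adds noise and leaves chance baseline imbalance in the estimate. With about 30 completers per arm and a Bonferroni correction to pay for, the lost precision matters.

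**Within-arm tests.** Women enter because a HOMA-IR reading was at or above 2.29. If that reading also serves as baseline, later readings tend to be lower on average even without treatment. A paired test counts that fall as change. With no untreated arm, nothing in the data shows how much of a within-arm fall would have happened anyway. The risk is greatest for Baduanjin alone, where a significant paired test could be read as proof that it works.

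**Working it through.** **Inputs** (protocol, Sample size calculation, unless stated)

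- Pilot metformin: "HOMA-IR decreased from 2.11±0.30 to 1.71±0.26 in the metformin treatment group", and "the difference before and after treatment was 0.40±0.24".
- Pilot BSHTD plus metformin: 2.09 (SD 0.30) to 1.52 (SD 0.26), change 0.57 (SD 0.27).
- Two-sided alpha 0.05; 30 evaluable and 38 enrolled per arm.
- Entry limit 2.29 (Inclusion criteria).

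**1. The plan's own sample size.** The article does not list the five means. Assume three arms at 0.40 and two at 0.57, with change variance (0.24² + 0.27²)/2 = 0.06525 (SD 0.255). The grand mean is 0.468 and the sum of squared deviations is 3 × 0.068² + 2 × 0.102² = 0.0347. The noncentrality at n = 30 is 30 × 0.0347/0.06525 = 15.9, and F-test power is 90.1%. Then 30/0.80 = 37.5, so 38 per arm and 190 in total. The stated figures reproduce under this pattern; other patterns with the same range need more (for example 45 per arm if one arm differs from four).

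**2. Baseline-to-post correlation.** r = (s₀² + s₁² − s_change²)/(2 s₀ s₁).

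- Metformin: (0.0900 + 0.0676 − 0.0576)/0.156 = 0.641.
- Combination: (0.0900 + 0.0676 − 0.0729)/0.156 = 0.543.

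**3. ANCOVA error variance, untruncated.** s₁²(1 − r²) = 0.0398 and 0.0477, mean 0.0437 (SD 0.209). Ratio to change-score variance: 0.0437/0.06525 = 0.67, a reduction of 33%.

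**4. The same, with the pilot distribution truncated at 2.29** (normality assumed). For metformin, the limit is (2.29 − 2.11)/0.30 = 0.60 SD above the mean. The truncated mean is 2.475 and SD 0.151; for the combination arm they are 2.470 and 0.148. The slope b = r s₁/s₀ is 0.556 and 0.471. Change variance = residual variance + (1 − b)² × truncated baseline variance:

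- Metformin: 0.0398 + 0.444² × 0.151² = 0.0443.
- Combination: 0.0477 + 0.529² × 0.148² = 0.0538.

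The mean is 0.0491 (SD 0.221). Ratio: 0.0437/0.0491 = 0.89, a reduction of 11%.

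**5. Power for BSHTD plus metformin against metformin** (difference 0.57 − 0.40 = 0.17, 30 per arm, noncentral t). The last column assumes that all ten pairs are corrected, so alpha = 0.005.

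| Baseline distribution | Analysis | SD | Power, alpha 0.05 | Power, alpha 0.005 |
|---|---|---|---|---|
| Untruncated | Change score | 0.255 | 72% | 38% |
| Truncated at 2.29 | Change score | 0.221 | 83% | 53% |
| Either | ANCOVA | 0.209 | 87% | 59% |

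**6. Regression to the mean within an inert arm.** Expected fall = (1 − r)(entry mean − source mean). If screened women resemble the pilot and the screening value is the baseline:

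- r = 0.641: 0.359 × (2.475 − 2.11) = 0.131; SD of change 0.237; paired test significant in 83% of trials at n = 30.
- r = 0.543: 0.457 × (2.470 − 2.09) = 0.173; SD of change 0.261; significant in 94%.

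Only 25–27% of such a population would qualify. Varying the source mean (SD 0.30) and r from 0.5 to 0.9:

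| Source mean | Fall with no effect | Paired test significant |
|---|---|---|
| 2.11 | 0.18 to 0.04 | 95% to 31% |
| 2.5 | 0.06 to 0.01 | 21% to 8% |
| 2.8 | 0.015 to 0.003 | about 6% to 5% |

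**7. Between-arm validity.** A simulation with no treatment effect (10,000 runs, r = 0.6, source mean 2.11, 30 per arm) gave 87% false positives for the within-arm test and 5.0% for the between-arm test on change.

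**The case against.** ANOVA on change is unbiased under 1:1:1:1:1 randomisation, and regression to the mean is equal across arms in expectation. This stands: the confirmatory comparison is not wrong, only less efficient, and the stated sample size is not in error.

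Covariate adjustment is often left to an analysis plan, and that document is not shown. This has limited force, because the article does not stay silent: it specifies comparisons on change and names unadjusted tests.

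The protocol does not rest efficacy on paired tests. All four assumptions in the Discussion are between-arm: BSHTD against metformin, BSHTD plus metformin against metformin, BSHTD plus Baduanjin against each component, and the two combinations against each other. This stands. A reader might infer that the paired tests are the only evidence on Baduanjin, but group C is also compared with the other arms, and BSHTD plus Baduanjin against BSHTD gives a randomised estimate of what Baduanjin adds. What no contrast gives is Baduanjin against no treatment, and ANCOVA would not supply it either.

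The large figures depend on assumptions. This also stands. The 33% saving uses a pilot baseline that the entry rule would largely exclude, while the high false-positive rates use that distribution truncated, where the saving is only about 11%. The two extremes should not be quoted together. The correlation comes from treated patients and may understate untreated test-retest correlation, which would inflate the expected fall. The protocol lists separate screening and baseline visits; the text does not say whether HOMA-IR is re-measured, which would shrink the effect. Finally, intention-to-treat analysis with imputation may bring the analysed number nearer 38 per arm than 30.

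**Conclusion.** The point holds as a correctable weakness in the analysis, not as a bias in the trial's main comparisons.

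**Between arms:** valid, but forgoing an error-variance reduction of about 11% to 33%. In power terms this is 83% or 72% against 87% for the one contrast the pilot informs, before Bonferroni correction. The range rests on the pilot SDs carrying over and on how far the entry limit narrows the baseline distribution.

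**Within arms:** the paired tests cannot separate treatment effect from regression to the mean. The false-positive rate in an inert arm may be near 5% if most screened women lie well above 2.29, or about 90% if they resemble the pilot and the screening value is the baseline. The documents do not settle where in that range the trial falls.

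A reader might go further and infer that selection on HOMA-IR makes the trial's efficacy findings spurious. The documents do not support that: the stated hypotheses are between-arm, and randomisation protects them.

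**What to change.** In the Statistical analysis section:

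1. Make the primary between-arm analysis an ANCOVA of end-of-treatment HOMA-IR on arm and baseline HOMA-IR, with the Bonferroni-corrected contrasts kept.
2. Report within-arm changes descriptively with confidence intervals, and state that no efficacy claim rests on them, including for Baduanjin alone.

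A log scale for HOMA-IR is optional and not needed for this point. The cost is a wording change before analysis. It uses data already collected and needs no extra visits, tests or participants.

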**Methods/design:**

This is a randomized controlled trial involving 190 participants diagnosed with IR-PCOS. All participants will be randomly allocated into 5 groups: group A will receive metformin; group B, BSHTD; group C, Baduanjin; group D, BSHTD combined with metformin; and group E, BSHTD combined with Baduanjin. One course of treatment lasts 3 months, a total of two courses. The primary outcomes are changes in the homeostatic model assessment of insulin resistance (HOMA-IR) and improvements in the oral glucose tolerance test (OGTT) and insulin-releasing test (INS). The secondary outcomes are improvements in the menstrual cycle, ovulation rate, clinical pregnancy rate, basic serum sex hormone levels, free androgen index (FAI), Ferriman-Gallwey scores, body mass index (BMI) and TCM syndrome scores. The related observation indexes will be collected at baseline, during the process of treatment and at the 6-month follow-up. Simultaneously, close monitoring of possible adverse events will be performed throughout the trial process.

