### Study-specific visits and procedures

All participants will receive 2 courses of treatment lasting for 6 months and will be followed up for 6 months. All participants will attend a total of 6 visits: screening visit, baseline visit, first course visit, end-of-treatment visit, and two follow-up visits. Simultaneously, close monitoring of possible adverse events during the trial process will be performed. A flowchart of this trial is depicted in Fig. 1. The schedule of trial enrolment, intervention and assessment is expounded in Table 1.

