### Imputation procedure for missing data

We will report the reasons for intervention withdrawal in different randomized subgroups and conduct a qualitative analysis of the reasons. The impact of any missing data on the study results will be assessed by sensitivity analysis of the augmented data sets. Patients who drop out of the trial will be enrolled in the analysis of missing data using modern imputation methods.

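### The stated comparison of baseline-to-end changes gives first-course values no role and names no baseline adjustment; a baseline-adjusted repeated-measures model would use both at little cost

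*Protocol article*

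**What the plan says.** All references are to the protocol article.

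- **Comparison.** Statistical analysis: "Comparisons will be processed based on changes from baseline to the end of the intervention and follow-up". Between-arm tests are ANOVA with Bonferroni correction, or Kruskal-Wallis followed by Mann-Whitney. No baseline covariate and no repeated-measures model is named.
- **Population.** The same section says that all participants' data enter the final analysis under intention-to-treat.
- **Visits.** Study-specific visits and procedures lists six: "screening visit, baseline visit, first course visit, end-of-treatment visit, and two follow-up visits". A course lasts three months, so the first-course visit falls at about month 3.
- **Data collected.** The Abstract, straight after listing the outcomes, says: "The related observation indexes will be collected at baseline, during the process of treatment and at the 6-month follow-up".
- **Dropouts.** Imputation procedure for missing data says that dropouts are brought in by modern imputation methods, otherwise unspecified. It gives the augmented data one use: "The impact of any missing data on the study results will be assessed by sensitivity analysis of the augmented data sets".
- **Attrition.** Sample size calculation allows for 20%, with no timing and no split by arm.

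**The concern.** A change score by ANOVA or a rank test needs an end value and cannot use an intermediate one. A woman seen at the first-course visit who then leaves contributes to such a comparison only if her end value is imputed, and imputation is tied in the text to a sensitivity analysis. The information she gave at month 3 then has no stated place in the main result, which fits poorly with an intention-to-treat analysis of everyone.

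Two things are at stake. One is precision: a change score without baseline adjustment is inefficient when baseline and end values are only moderately correlated. The other is protection against selective dropout. Participants are not blinded, and the arms differ in burden (tablets, a twice-daily decoction, daily exercise, combinations). Dropout that differs by arm and depends on early response is therefore plausible, although nothing in the article shows that it will happen.

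**Working it through.** **1. The plan's own figure.** 30 / (1 − 0.20) = 37.5, rounded up to 38 per group; 5 × 38 = 190. This matches. A loss of 20% leaves 38 × 0.8 = 30.4 per group, so even a completers' analysis keeps the planned 30.

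**2. Baseline-to-end correlation implied by the pilot.** Inputs from Sample size calculation: baseline SD 0.30 and end SD 0.26 in both groups. For metformin "the difference before and after treatment was 0.40±0.24"; for the decoction plus metformin the change is 0.57 with SD 0.27. With r = (SD₀² + SD₁² − SD_change²) / (2 × SD₀ × SD₁):

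- metformin: (0.0900 + 0.0676 − 0.0576) / 0.156 = 0.64
- combination: (0.0900 + 0.0676 − 0.0729) / 0.156 = 0.54

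**3. Change score against baseline adjustment.** The adjusted variance is SD₁² × (1 − r²):

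- metformin: 0.0676 × (1 − 0.411) = 0.0398, against 0.0576 for the change; ratio 1.45, a 31% cut
- combination: 0.0676 × (1 − 0.295) = 0.0477, against 0.0729; ratio 1.53, a 35% cut

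The planned change score thus has about 1.5 times the variance of a baseline-adjusted comparison, before any month-3 data are used.

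**4. What month-3 values add to precision.** Assumptions, not in the article: dropout is equal across arms and non-informative; either all or half of the dropouts have a month-3 value; correlations are 0.6 throughout, or 0.65 (baseline–month 3), 0.75 (month 3–end) and 0.60 (baseline–end).

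Relative to completers' ANCOVA, the gain in effective sample size is 1 / (1 − p² × m). Here p is the month-3-to-end correlation given baseline, and m is the share of women seen at month 3 who lack an end value (0.20 if all dropouts are seen then, 3.8/34.2 = 0.11 if half are).

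- p = (0.60 − 0.36) / (1 − 0.36) = 0.375: gain 1.03 (all) or 1.016 (half)
- p = (0.75 − 0.39) / √(0.5775 × 0.64) = 0.59: gain 1.075 (all) or 1.04 (half)

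Simulation under the same assumptions gave 1.015 to 1.09.

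**5. Bias in one assumed scenario.** Simulation of 6000 trials with 38 per arm and a true difference of 0.17 (0.57 − 0.40). SDs were 0.30, 0.28 and 0.26 at baseline, month 3 and end (the month-3 SD is assumed), with the two correlation sets above. Dropout was assumed to be 28% in the metformin arm and 12% in the combination arm, driven by a latent variable correlated 0.6 with poor month-3 response.

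| Analysis | Mean estimate (two correlation sets) |
|---|---|
| Completers, change score | 0.149 / 0.145 |
| Completers, ANCOVA | 0.159 / 0.155 |
| Likelihood model using month 3 | 0.170 / 0.171 |

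The change score falls short by 0.021 to 0.025, or 12 to 15%. With pooled SD 0.255, the standard error is 0.255 × √(2/30.4) ≈ 0.065, so the shortfall is 0.32 to 0.38 of a standard error. ANCOVA alone recovers 0.010 of it, roughly 40 to 50% of the correction. If half the dropouts leave before month 3, the figures are 0.143–0.148 for the change score and 0.164–0.165 for the model. With equal dropout unrelated to response, there is no bias.

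**The case against.** A reader might infer that women who leave after month 3 are excluded from the main comparison and that the result will therefore be biased. The article supports neither step. It promises intention-to-treat on all participants and says that dropouts are brought in by imputation. Imputation that includes the month-3 value rests on the same missing-at-random assumption as a repeated-measures model and would give similar answers. Whether it does include that value is detail that an article may leave to the full protocol or analysis plan.

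Further points stand:

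- The schedule table is not shown, so measurement of HOMA-IR, OGTT or insulin at the first-course visit is unconfirmed. The Abstract suggests it but names no outcome for that visit.
- The bias figures depend wholly on assumed differential, response-related dropout, and their comparator is a completers' analysis that the article never names as such. The shift is toward the null and small against the standard error.
- A sizeable part of the correction comes from baseline adjustment, not from month-3 data. The proposed model is itself slightly off when some women leave before month 3.
- Enrolling 38 per group already covers the planned loss in numbers.

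The objection does not remove the method that the section does state: between-arm tests on changes with no covariate named. That is a choice made in the text. A repeated-measures model uses more of the data already scheduled, and inflating enrolment does not protect against selective dropout.

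**Conclusion.** The point holds as one about the choice of method and unclear wording, not as a demonstrated bias. First-course values have no stated role, and the main comparison appears to use observed end values, since the augmented data are assigned only to a sensitivity analysis.

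The best-supported gain is from baseline adjustment: about a third less variance for HOMA-IR, if the pilot correlation of 0.54 to 0.64 carries over. The pilot baselines (2.11 and 2.09) lie below the trial's entry threshold of 2.29, so the correlation in this trial may differ. Month-3 values add a modest 1.5 to 9% under the assumed correlations and timing of dropout, plus protection if dropout depends on early response. Whether any bias exists, and how large it is, cannot be computed from the article; the 0.02 to 0.025 shortfall illustrates one assumed scenario.

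**What to change.** For HOMA-IR and every other continuous outcome that the schedule measures at the first-course visit, make the main analysis a repeated-measures model with arm, visit, arm-by-visit and baseline, and an unstructured covariance. Read the arm contrasts at end of treatment. Keep imputation as the sensitivity analysis. For continuous outcomes not measured at that visit, replace the change-score ANOVA with ANCOVA adjusted for baseline. State in the Statistical analysis section whether the main comparison uses observed or imputed values, and in the imputation section whether first-course values enter the imputation model.

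The cost is revised wording and a little more programming, with no new visits or data. The downside is a modelled covariance, which is minor with so few visits. The rank-test route for non-normal outcomes would also need a matching statement, because this model does not replace it automatically.

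### A normality check on the trial's own data chooses between two different analyses of HOMA-IR, only one of which matches the power statement and carries a stated multiplicity correction

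*Protocol article*

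**What the plan says.** The Primary outcomes section lists the change in HOMA-IR together with the glucose tolerance and insulin-releasing tests. The Sample size calculation calls HOMA-IR the most important of the outcomes and sizes the trial by a one-way ANOVA F test on means: 30 evaluable patients per arm, 150 in all, for 90% power at the 5% level, raised to 38 per arm for 20% attrition.

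The Statistical analysis section states that "Comparisons will be processed based on changes from baseline to the end of the intervention and follow-up". It then sets up a preliminary check: "The one-sample Kolmogorov-Smirnov test and graphical methods will be applied to test the normal distribution of continuous variables", with HOMA-IR in the list of examples. The result of the check fixes two things:

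- The summary, "which will be presented as the mean ± standard deviation if normally distributed and as the median with an interquartile range if not normally distributed".
- The between-group test. ANOVA with Bonferroni correction "will be carried out to compare differences among groups of continuous variables consistent with a normal distribution"; otherwise, "Continuous variables that do not meet the normal distribution will be processed by using the Kruskal-Wallis test followed by the Mann-Whitney" U test. No correction is named on this second route.

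The section closes by tying significance to a two-tailed 5% level and a mean difference with its 95% confidence interval.

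**The concern.** A primary analysis should be fixed before the outcome is seen. Here the stated rule leaves it to a preliminary test, and the two routes are not interchangeable.

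1. ANOVA compares mean changes. Kruskal-Wallis and Mann-Whitney compare ranks. The quantity estimated therefore depends on the check.
2. The power statement covers the F test on means only. If the rank route is taken, the trial runs an analysis for which it was not sized.
3. The rank route does not supply the mean difference and interval that the same section requires. Two of the working assumptions in the Discussion are of equal effect (B with A, and E with D). Those can be judged only from an interval for a difference on a known scale.
4. Bonferroni is named on one route and nothing on the other. A normality check thus also decides how strictly the pairwise comparisons are judged.

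**Working it through.** **The plan's own figure.** Inputs from the Sample size calculation: pilot change 0.40 (SD 0.24) on metformin and 0.57 (SD 0.27) on decoction plus metformin.

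- Pooled SD = √[(0.24² + 0.27²)/2] = √0.06525 = 0.2554.
- Only two arm means are given. Assume three arms at 0.40 and two at 0.57; the grand mean is then 2.34/5 = 0.468.
- Σ(μ − 0.468)² = 3 × 0.068² + 2 × 0.102² = 0.03468.
- Noncentrality = 30 × 0.03468 / 0.06525 = 15.94 on 4 and 145 df, giving power 0.901. The smallest n reaching 90% is 30.
- Attrition: 30/0.8 = 37.5, so 38 per arm and 5 × 38 = 190.

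The stated size is reproduced, for the ANOVA route and this pattern of means. With the other three arms at the midpoint, power is 0.50.

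**What the correction does to D v A.** Five arms give 10 pairs. Taking Bonferroni over all of them (an assumption), each pair is tested at 0.05/10 = 0.005. The standard error is 0.2554 × √(2/30) = 0.0660, so the standardised difference is 0.17/0.0660 = 2.58. By normal approximation, power is 0.73 at the 0.05 level and 0.41 at 0.005.

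**Branch against branch, rules as written.** Simulated trials: 30 per arm, the means above, changes scaled to SD 0.2554, 1,500 trials per shape. The protocol gives no shape, so all five are assumptions. Mann-Whitney is uncorrected and follows a significant Kruskal-Wallis test.

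| Shape of the change | ANOVA and Kruskal-Wallis disagree | D v A power, Bonferroni | D v A power, uncorrected Mann-Whitney | D v A verdicts differ |
|---|---|---|---|---|
| Normal | 4% | 0.38 | 0.65 | 27% |
| Lognormal, log-SD 0.3 | 6% | 0.40 | 0.75 | 36% |
| Lognormal, log-SD 0.5 | 8% | 0.41 | 0.85 | 44% |
| Lognormal, log-SD 0.7 | 12% | 0.44 | 0.95 | 51% |
| t, 4 df | 8% | 0.42 | 0.81 | 39% |

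A separate run under assumed lognormal data put the last column at 32-35%.

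**Branch against branch, same correction on both.** With HOMA-IR itself assumed lognormal (log-SD 0.3-0.5), entry at 2.29 or more, decreases of 20% and 30% and 30 per arm, ANOVA and Mann-Whitney disagreed on D v A in 11.7%, 9.5% and 5.6% of 2,000 trials per setting. The separate run gave 8-10%.

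**Error rates.** Type I error of the overall test, check included, was 0.046-0.056. Familywise error across pairs when only some arms differ (normal data, 4,000 trials) was 0.017-0.026 with Bonferroni and 0.16-0.17 for Kruskal-Wallis followed by uncorrected Mann-Whitney.

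**The case against.** A normality check followed by a parametric or rank test is a common rule, it is stated in advance, and the analysts are blinded to allocation, so the choice cannot be steered towards an arm. Two valid tests will always disagree in some trials near the threshold. When four readings of the Kolmogorov-Smirnov check (fixed or estimated parameters, pooled or by arm) were applied to the same simulated trials, the overall conclusion changed with the reading in only 1-7% of them. The D v A conclusion changed in 2-16% with Bonferroni on both routes, and in 6-37% with it on one. All of this stands, and it limits the size of the harm. It does not remove the mismatch between the rank route and the plan's own power statement and required estimate.

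Three stronger readings are tempting and are not supported:

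- *The check turns on unstated details rather than on the data.* It depends on both. Strong skew is nearly always flagged by either pooled reading, and normal data are almost never flagged with fixed parameters. Graphs are part of the check. The exact variant of the test may also be in an analysis plan that is not shown, so its absence here is no fault.
- *The entry rule makes HOMA-IR non-normal by design.* The rule "A value ≥2.29 [17] is considered to be indicative of IR" cuts off baseline values, but the comparisons are of changes, which it does not truncate.
- *Imputed data sets may fall on different sides of the check.* The missing-data section mentions only modern imputation methods and "sensitivity analysis of the augmented data sets". It does not state multiple imputation or a check repeated in each set.

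**Conclusion.** The point holds as a fault in a stated rule: a preliminary check chooses the test, the summary, the quantity compared and, as written, the multiplicity control for the outcome on which the trial was sized. Under assumed skewed data, the D v A verdict differs between routes in roughly 6-12% of trials at a common corrected level and in about a third if Mann-Whitney is left uncorrected (27-51% over the shapes in the table). The common-level figure belongs to its own simulation setting; the 16% upper end for differing readings of the check shows that it can be larger for other shapes.

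A reader might infer that the trial's false-positive rate is inflated overall. For the test across all five arms it is not. The inflation is confined to pairwise comparisons on the uncorrected rank route, and it disappears if the full plan applies the correction there too. The sizes rest on assumed distributions, on assumed means for three arms and on Bonferroni over all 10 pairs. The choice of analysis from the data does not depend on any of these. It should be changed, but it does not undermine the design.

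**What to change.** Drop the normality check as a selector for HOMA-IR. Name one primary analysis of the change in HOMA-IR: a linear model with all five arms, preferably adjusted for baseline, on a scale stated now. Log HOMA-IR is a natural candidate, because the index is a product of glucose and insulin and the planning target is a percentage fall. State the contrasts (the Discussion points to D v A, E v B, E v C, B v A and E v D), their 95% confidence intervals and one multiplicity rule. Use the model whatever the distribution looks like, and inspect residuals by plots. Report Kruskal-Wallis and Mann-Whitney, with the same correction, as a sensitivity analysis only.

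The cost is analysis wording. On the raw scale the stated sample size is unaffected (power 0.901 with 30 per arm under the means above). On the log scale, effects become ratios: falls of 30% and 20% correspond to 0.70/0.80 = 0.875, and power should be restated on that scale. The small downside is that the model is kept even if residuals look imperfect. With about 30 per arm, contrasts of means tolerate this reasonably well, and the rank results stand beside them.
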